A WFPBD emphasizing vegetables, fruits, grains, and legumes, while omitting animal products, and limiting saturated fat intake has recently been shown to reduce diabetes related PNP severity and symptomology (19, 21, 22, 29, 30). In a cohort study assessing a WFPBD in 21 participants with type 2 diabetes, a statistically significant reduction of both serum triglycerides and total cholesterol, alongside a noticeable decrease in pain, weight, and insulin requirements was reported (22). Likewise, data from over 110 observational and clinical trials suggest that dietary patterns similar to a WFPBD are associated with a decreased presence of diabetes and significant improvements in biochemical profiles, including total LDL, and therapeutic requirements, for insulin in particular (21). Finally, a comprehensive randomized control trial seeking to address neuropathic pain management in 34 participants with neuropathy due to diabetes corroborates previous findings. Using both subjective questionnaire and objective quantitative sensory testing (QST), and electrophysiology, a significant decline in weight, body mass index (BMI), and glycemia was observed alongside a statistically significant improvement in neuropathic pain (19). Overall, WFPBDs have proven to be effective in the management of neuropathy due to diabetes, limiting endoneural ischemia, and providing sufficient glycemic control and lipid management, which when uncontrolled seem to exacerbate neuropathic pain. As a result, this phenomenon may translate to the management of PNP in leprosy, where diabetes comorbidity is common, and research has shown that diet and lifestyle interventions may be sufficient to control such steroid-induced hyperglycemia (23–28, 30–32). A WFPBD may also provide enhanced nutritional and antioxidant intake, conferring neuro-protective effects against leprosy alone while patients are actively undergoing antimicrobial MDT.

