#### 2.6.2. Continuous and categorical variables

Descriptive statistics including reported means ± standard deviation for continuous variables [questionnaires including MNSI-physical assessment, Neuropathy Total Symptom Score (NTSS), modified Medical Research Council Scale (mMRCS), Neuropathic Pain Symptom Inventory (NPSI), McGill Pain Questionnaire (MPQ), Pittsburgh Sleep Quality Index (PSQI), and International Physical Activity Questionnaire (IPAQ) summative scores, visual analog scale (VAS), anthropometrics, diabetes duration, hemoglobin A1c, and serum micronutrient levels] and proportions for categorical variables [number of adverse events, dietary adherence, insulin use, leprosy clinical status (according to the WHO and Ridley Jopling classification systems), frequency and prevalence of inflammatory leprosy reactions, corticosteroid use] will be reported by each study group (57). Between- and within-group comparisons will also be made for continuous variables using the Student’s *t*-test with reported *p*-values, and for categorical variables using the chi square or Fisher’s exact tests, reporting *p*-values with odds ratios and 95% confidence intervals. Statistics will also be reported for all time points including baseline, and end of study. Multivariate logistic regression adjusting for covariates [such as age, sex, PROGRESS+ factors (58, 59), level of physical activity, smoking status, alcohol consumption, comorbidities, diabetes status] and potential effect modifiers (such as change in weight over time, medication de-escalation over time) will be carried out to ascertain the impact of a WFPBD on PNP in leprosy patient sub-populations and under various conditions. All statistical analysis will be carried out using GraphPad Prism 8 (GraphPad, United States).

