### 3.3. Secondary outcomes

#### 3.3.1. Anthropometrics, sleep quality, physical activity, and diabetes control

As a dietary lifestyle intervention can have a drastic effect on anthropometrics, height and weight will be measured at both baseline and at the end of the study and will be used to calculate body mass index (BMI) (Figure 3). Likewise, sleep quality has been associated with neuropathy severity, and must be monitored throughout the trial. The Pittsburgh Sleep Quality index is a validated questionnaire, widely used to assess sleep perturbation due to various etiologies. Participants can be assigned a maximum of 21 points indicating severe difficulties in all areas of sleep quality (67). The PSQI will be collected at baseline and at the end of the study. Self-reported physical activity will also be collected at such intervals using the International Physical Activity Questionnaire. The IPAQ includes 27-items designed to gauge the frequency and intensity of physical activity carried out in a 7-day period, encompassing occupational, transportation, housework, and leisure activities. It has been extensively tested and validated throughout 12 countries and has previously been utilized in assessing self-reported physical activity in both diabetes and leprosy cohorts (68–70). To avoid the potentially confounding effects of additional lifestyle levers, such as sleep quality and exercise, these assessments are paramount during downstream analysis. Lastly, in individuals experiencing a biochemical diabetes due to leprosy related corticosteroids, an assessment of diabetes control including duration of illness, therapeutics used, and insulin status will also be carried out to monitor any changes throughout the trial (Figure 3). Standard biochemistry, including serum cholesterol, triglycerides, hemoglobin-A1c, serum glucose, hepatic transaminases, creatinine, and basic micronutrient panel (e.g., serum ferritin, B12) will be taken to measure diabetes parameters and general physiological status. To better ascertain the relationship between the dietary lifestyle intervention and leprosy itself, neuropathy and neuropathic pain outcomes will be stratified by secondary outputs, with specific emphasis on diabetes status, and steroid use.

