### 3.4. Potential stratifiers/confounders

Beyond primary and secondary endpoints, potentially confounding variables will be collected and utilized for downstream data analysis including: (1) demographic data: age, sex, socioeconomic status [relative within country and absolute according to World Bank definitions (75)], occupation (considering level of manual work, repetitive tasks, and prolonged standing/walking/climbing), household membership (living alone vs. with family members), and education level; and (2) lifestyle-related information: level of physical activity (via the international physical activity questionnaire), tobacco and cannabis smoking and alcohol consumption habits (amount consumed/day), and environment (urban vs. rural; meters a.s.l.). Effect modifiers including weight loss over time and de-escalation of medication over time will also be considered. Considerations of intervention cost, feasibility, cultural acceptability, and adherence will also be collected and summarized in a thematic analysis (Figure 3).

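### The regression for the diet effect conditions on weight change and medication de-escalation, both of which arise after randomisation, so it does not estimate the total effect of the diet

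*Protocol article*

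**What the plan says.** Section 2.6.2 specifies "Multivariate logistic regression adjusting for covariates" (age, sex, physical activity, comorbidities, diabetes status and others), and the same sentence adds "potential effect modifiers (such as change in weight over time, medication de-escalation over time) will be carried out". The stated aim is "to ascertain the impact of a WFPBD on PNP in leprosy patient sub-populations and under various conditions".

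Section 3.4 lists the two terms again: "Effect modifiers including weight loss over time and de-escalation of medication over time will also be considered".

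Section 3.3.1, under secondary outcomes, says that "neuropathy and neuropathic pain outcomes will be stratified by secondary outputs, with specific emphasis on diabetes status, and steroid use". On sleep and exercise it says: "To avoid the potentially confounding effects of additional lifestyle levers, such as sleep quality and exercise, these assessments are paramount during downstream analysis". Height, weight, the sleep index and the activity questionnaire are all measured at baseline and at study end.

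The article also says that the diet moves some of these variables. Section 3.3.1 gives as its reason for measuring weight: "As a dietary lifestyle intervention can have a drastic effect on anthropometrics". The Introduction reports of a randomised trial in diabetic neuropathy that "a significant decline in weight, body mass index (BMI), and glycemia was observed", and of a 21-participant cohort that weight and insulin requirements fell.

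Separately, section 2.6.2 plans unadjusted between-group comparisons: Student's t-test for continuous variables, and chi-square or Fisher's exact tests for categorical ones.

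**The concern.** Randomisation makes the arms comparable on what exists before allocation. Weight change and medication de-escalation over 24 weeks come afterwards, and by the article's own account the diet is expected to change at least weight and insulin need. Two things follow from placing them in the model.

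First, the treatment coefficient becomes a comparison at equal weight change and equal de-escalation. That removes whatever part of the benefit works through those routes, and the article offers metabolic improvement as part of the mechanism.

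Second, participants who lose weight on the diet and those who lose weight in the control arm are not randomised counterparts. They may differ in illness, appetite, activity or adherence, and such differences can shift the estimate either way. Calling the variables effect modifiers does not help: a subgroup or interaction defined by an on-study change has the same defect. A modifier has to be fixed before treatment can act on it.

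At stake is the only covariate-adjusted estimate of the diet effect that the article describes, together with any subgroup claims drawn from it.

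**Working it through.** No figure in the article is disputed, so the main check is one of timing.

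| Variable | Where used | Timing in the text | Expected to respond to the diet? |
|---|---|---|---|
| Weight change | 2.6.2, 3.4 | Change over time, so after randomisation | Yes (1, 3.3.1) |
| Medication de-escalation | 2.6.2, 3.4 | Change over time, so after randomisation | For insulin need (1); other drugs not stated |
| Diabetes status, steroid use | 3.3.1 strata; diabetes status also a 2.6.2 covariate | Not restricted to baseline | Possible if taken on study; not if taken at baseline |
| Sleep, activity | 3.3.1; activity also a 2.6.2 covariate | Measured at baseline and study end; time of use not stated | Possible if taken on study; not if taken at baseline |

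Only the first two rows are post-randomisation by definition. For the others the fault is that the time point is left open.

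**Illustration of the mechanism.** In a linear model,

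adjusted effect = total effect − γ × δ,

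where δ is the between-arm difference in weight change and γ is the within-arm slope of the outcome on weight change.

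Inputs from section 2.6.1:
- Total effect: 5.3 − 7.1 = −1.8 questionnaire points.
- Pooled SD: √((2.5² + 2.8²)/2) = 2.654.

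Assumptions, none of them in the article:
- δ = −1 SD of weight change.
- A share s of the effect runs through weight, so γ = 1.8 × s when weight change and pain have no common cause.

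The adjusted effect is then −1.8 × (1 − s):

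| Assumed share s | Adjusted for weight change | Simulated, split at a weight-loss cut |
|---|---|---|
| 0% | 1.80 | 1.80 |
| 25% | 1.35 | about 1.5 |
| 50% | 0.90 | about 1.2 |
| 75% | 0.45 | about 0.95 |

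(Sizes in points; all favour the diet. The simulation used 400,000 subjects per scenario.)

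Now add an unmeasured common cause of weight change and pain, with loading ±0.3 on weight change and 0.5 × 2.654 = 1.327 on the outcome. It adds ±0.3 × 1.327 = ±0.40 to γ. With no mediation at all, the adjusted effect is 1.8 − 0.4 = 1.4 or 1.8 + 0.4 = 2.2; the simulation gave 1.42 and 2.21. So the direction of the bias is not determined.

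**The case against.** The strongest reply is that the main comparison is untouched. The between-group t-tests and the chi-square or Fisher's tests do not condition on weight or medication, and the sample size rests on an unadjusted two-group comparison. The regression is aimed at sub-populations and varying conditions, so it can be read as supplementary, and section 3.4 commits only to considering the modifiers. This stands, and it limits the point to the regression and the stratified results.

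A reader might infer more in four ways.

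- **That the trial loses power.** Putting the attenuated effects into a two-sample formula at 30 per arm (SD 2.654, two-sided 5% assumed) takes power from 75% to 50%, 26% and 10%. That describes a test of an attenuated effect under assumed shares. The power of the unadjusted comparison does not change.
- **That a benefit in pain medication is hidden.** The text says only medication, and the supporting evidence concerns insulin. Section 2.4.2 also tells both arms to continue leprosy therapeutics as prescribed. Section 2.6.2 already reports anthropometrics, insulin use and corticosteroid use by group.
- **That all the stratifiers are mediators.** Diabetes status, steroid use, sleep and activity can be taken at baseline, and section 2.3 treats steroid-induced diabetes as something present at eligibility. Used that way they are acceptable.
- **That the diet effect will be understated.** The common-cause cases show that it could equally be overstated.

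The numbers are also weak as evidence of size: the model is linear where the plan is logistic, and the coefficients largely restate the assumed share.

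What the reply does not answer is that two named variables are post-randomisation by their own wording and are written into the adjustment set in one section and repeated in another. That is a stated choice, not a detail left to an analysis plan.

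**Conclusion.** The point holds for the regression in 2.6.2, for effect modification as described in 3.4, and for stratification in 3.3.1 wherever on-study values are used. Estimates that condition on weight change or medication de-escalation do not target the total randomised effect of the diet and may err in either direction.

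For the remaining stratifiers the finding is narrower: their time point is not restricted to baseline. The documents give no mediated share, no expected weight difference between arms and no information on common causes, so no size can be predicted; the attenuation figures show the mechanism only. A claim that the trial's main result is biased would not be supported.

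**What to change.** - **2.6.2 and 3.4:** remove weight change and medication de-escalation from the adjustment and effect-modifier set. State that all covariates take their baseline values.
- **3.3.1:** restrict stratification to baseline values, for example BMI, diabetes status, corticosteroid use, and the activity and sleep scores. Test effect modification by treatment-by-baseline interaction.
- **Outcomes:** report weight change and medication de-escalation by arm. Reporting of anthropometrics, insulin use and corticosteroid use by group is already planned, so the addition is mainly a definition of de-escalation for analysis.
- **Mediation:** if the route through weight or medication is of interest, present it as a separate analysis labelled exploratory, with its assumptions stated, and never in place of the total effect.

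The cost is a wording change. The outcome measures are already scheduled at baseline and study end, and no extra visits or participants are needed. It should be made before outcome data are seen.

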## 3. Projected outcomes

### 3.1. Data collection

Outcomes will be collected at both baseline and at study end by dedicated personnel blinded to group allocation. Data will be housed on a password-protected and encrypted database generated on a secure drive which will be locked in the respective study centres. Prior to database entry, all patient and study data will be anonymized, and a master list linking patient identification and consecutive study numbers will be generated, secured, and housed separately to said database and to which only the study investigators will have access. Data collected for this study cannot be linked to a specific patient, and the principal investigator and study researchers will be the only individuals who have access to this information. Following final data collection, data will be pooled across study centres and analysis will be conducted within the research lab of the principal investigator.

### 3.2. Primary outcomes

#### 3.2.1. Michigan neuropathy screening instrument

The MNSI is a robust assessment of neuropathy identifiers that includes both a subjective questionnaire and objective measurements of perception via QST. Specifically, Semmes-Weinstein monofilaments will be used to measure sensation at the ulnar nerve-innervated dorsum of the hand bilaterally, given this site’s predilection for leprosy associated nerve damage, while a 128 Hz tuning fork will be utilized to test for vibration perception thresholds at the great toe (43, 60). This screening instrument has been widely used and validated in both diabetes and leprosy related neuropathy cohorts (19, 60). Scoring is based on a binomial yes/no response to specific questions where yes = 1 point and no = 0 points. Additionally, any abnormal QST result = 1 point, and a score of 4 or greater indicates the presence of neuropathy (60). The MNSI will be conducted at both baseline and at study end and will be utilized as one of the measurements for sensory neuropathy (Figure 3).

**Figure 3 fig3:**
[figure not shown]
Outcomes, stratifiers, and additional considerations to be collected. AE, adverse events; BMI, body mass index; IPAQ, international physical activity questionnaire; mMRC, modified medical research council scale; MNSI, Michigan neuropathy screening instrument; MPQ, McGill pain questionnaire; NPSI, neuropathic pain symptoms inventory; NTSS, neuropathy total symptom score; PA, physical activity; PSQI, Pittsburgh sleep quality index; RRS, resonance Raman spectroscopy; Stnd, standard of care; VAS, visual analog scale; WFPBD, whole foods plant-based diet.

#### 3.2.2. Neuropathy total symptom score

The Neuropathy Total Symptom Score will also be used to formulate a more robust assessment of sensory neuropathy. Unlike the MNSI, the NTSS includes considerations for both neuropathy intensity and frequency. Based on a summative questionnaire, participants can be assigned a maximum of 21.96 points, indicating greater morbidity, and depicted as a matrix comparing neuropathy intensity (mild, moderate, severe) versus frequency (occasional, often, continuous) (61). This questionnaire has been widely used and validated in cohorts of individuals with diabetes, a common comorbidity of leprosy, and will strengthen the assessment of sensory neuropathy within this trial (23, 61). The NTSS will be carried out at both baseline and study end (Figure 3).

#### 3.2.3. Modified medical research council scale

The modified Medical Research Council Scale is a reliable tool that has been commonly used to measure motor neuropathy in patients with leprosy (43). The mMRCS utilizes voluntary muscle testing (VMT) in the assessment of motor nerve function including the facial, ulnar, median, radial, and later popliteal nerves. Patients can be assigned a maximum of 5 points, which may be downgraded by any significant reduction of VMT. A score of less than 5 is indicative of decreased motor nerve function (43). The mMRCS will be utilized at baseline and at the end of study to provide a robust assessment of motor neuropathy in this trial (Figure 3).

#### 3.2.4. Neuropathic pain symptom inventory

The Neuropathic Pain Symptom Inventory incorporates both measures of pain intensity and frequency including common patient pain descriptors such as burning, squeezing, pressure, and stabbing relative to the past 24 h (62). It has most commonly been used in the assessment of neuropathic pain in leprosy cohorts, wherein the higher the score the greater the pain, out of a possible 100 points (62–64). Participants will complete the NPSI questionnaire as part of a comprehensive neuropathic pain assessment at both baseline and at the end of the study (Figure 3).

#### 3.2.5. McGill pain questionnaire

The McGill Pain Questionnaire will also be used to assess neuropathic pain throughout the trial, given a more robust set of patient pain descriptors. The MPQ classifies over 75 words into 4 descriptive pain categories including sensory, affective, evaluative, and miscellaneous, each with subcategories utilizing a scaled point system to indicate relative severity within each group, as well as over time. A maximum score of 78 points is possible, indicating most chronic and severe pain (65). This questionnaire has been utilized and validated within both diabetes and leprosy cohorts (19, 66). Alongside the NPSI, the MPQ will also be completed at both baseline and at the end of the study to provide the most comprehensive assessment of neuropathic pain possible (Figure 3).

#### 3.2.6. Visual analog scale

Participants will also subjectively assess pain level on a 10-cm Visual Analog Scale between absolute poles of “No pain” and “Worse possible pain,” both at baseline and at the end of the study. The VAS is a tool commonly used to assess pain given any underlying etiology, including both diabetes and leprosy, and is often utilized as the gold-standard when validating novel questionnaires assessing pain (19, 62, 63).

#### 3.2.7. Safety, tolerability, harms, adherence

Additional considerations concerning the longstanding implementation of a WFPBD within this population will also be assessed at each counseling session. Data on safety via the number of adverse events, tolerability via drop-out rate, and emerging harms, against gold standard PNP therapeutics (or non-interventions, such as watchful waiting) will be collected and summarized. Dietary adherence reported as a proportionate yes/no will also be collected to ensure interventional feasibility. Based on the current landscape of the literature a WFPBD is expected to perform as well, if not better, than the current standard of care when considering implementation (19, 47, 55) (Figure 3).

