#### 2.4.2. Lifestyle counseling

Participants in the intervention group will be instructed to follow a WFPBD for 24 weeks. The study duration was chosen as a conservative estimate of comparable lifestyle-based interventional trials that demonstrated statistically significant improvements in diabetes-related neuropathy outcomes (18, 19). The diet will emphasize vegetables, fruits, whole-grains, nuts, and legumes, while omitting animal products, and limiting fat intake (Table 2). Selection of specific plant-based components may differ across study sites in concordance with local culinary preferences and cultural practices related to food. By tailoring the diet to the unique cultural diaspora affected by leprosy, many of which already endorse plant-based components, we seek to enhance adherence and acceptability to the diet overall. Likewise, current economic projections suggest that diets seeking to reduce animal products are more affordable than current standard diets across all socioeconomic levels – particularly due to inclusion of global staples such as tubers, beans, legumes, and rice – further enhancing accessibility (48–50). Participants will receive weekly support and guidance via 1 h counseling sessions with registered dieticians or the equivalent at each participating site. Sessions will be designed to disseminate comprehensive guidelines for following the WFPBD including culturally acceptable recipes and addressing concerns or knowledge gaps regarding the intervention. Participants in both the intervention group, and control group will be instructed to continue their respective leprosy therapeutics as prescribed throughout the duration of the study. Finally, dietary adherence will be measured via monthly random 24 h dietary recalls, and participants are free to withdraw at any point during the trial if they no longer wish to participate.

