#### 2.5.2. Consent, randomization, and blinding

Patients with a history of leprosy will be pre-screened for inclusion via clinical records prior to routine follow up. Study personnel will approach eligible patients experiencing active or treated (“cured”) leprosy, as well as subjective neuropathic pain at participating tropical disease institutions. Eligible participants will receive a comprehensive in-person review of the trial protocol, including data collection requirements, and will be given the patient consent form. Patients will voluntarily confirm willingness to participate and will be free to withdraw at any point. Upon consent to enrolment, participants will be randomized to either the WFPBD intervention group, or standard of care control group. To ensure equal distribution and matching between study groups, randomization will be carried out using a stratified block method (52). Participants will be assigned to strata primarily by study site, followed by sex (male/female), and lastly age-band (18–65, >65) (Figure 2). Random sequence generation will be carried out using a computer-generated allocation sequence. Study investigators, physicians, and participants will not be blinded to group allocation due to the transparent nature of the dietary intervention and counseling. However, primary end points will be collected by independent study personnel, blinded to group allocation, allowing for a single-blinded protocol.

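### Adverse events are to be assessed at diet counselling sessions, which conflicts with the promised blinded collection and would bias the between-arm comparison if those events enter it.

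*Protocol article*

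**What the plan says.** All references are to the protocol article.

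- **Status of the outcome.** The abstract names safety, tolerability and harms among the primary outcome measures, and section 3.2.7 stands under 3.2 Primary outcomes. Section 2.2 places a limited side-effect profile among the secondary objectives.
- **When it is assessed.** Section 3.2.7 says these considerations "will also be assessed at each counseling session".
- **What is measured.** The same section describes "Data on safety via the number of adverse events, tolerability via drop-out rate, and emerging harms, against gold standard PNP therapeutics", or against non-intervention.
- **What the sessions are.** Section 2.4.2 opens with "Participants in the intervention group will be instructed to follow a WFPBD for 24 weeks" and continues: "Participants will receive weekly support and guidance via 1 h counseling sessions with registered dieticians or the equivalent at each participating site". On content it says: "Sessions will be designed to disseminate comprehensive guidelines for following the WFPBD". Section 2.5.2 gives the counselling as one reason why investigators, physicians and participants cannot be blinded.
- **What is promised on blinding and timing.** Section 2.5.2 says "primary end points will be collected by independent study personnel, blinded to group allocation". Section 3.1 says "Outcomes will be collected at both baseline and at study end by dedicated personnel blinded to group allocation".
- **How the data are analysed.** Section 2.6.2 reports, by study group, "proportions for categorical variables [number of adverse events, dietary adherence, insulin use" and further items. It compares categorical variables between groups by chi-square or Fisher's exact test, with odds ratios and 95% confidence intervals.

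**The concern.** The contact at which adverse events and emerging harms are elicited is also the contact that delivers the intervention. The comparator is standard of care, and no counselling is described for it. Two things follow.

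First, the sections cannot all be followed. Anyone recording events at a session that teaches the diet will in all likelihood know the allocation, yet sections 2.5.2 and 3.1 promise blinded collection.

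Second, if events gathered at the sessions are compared with whatever is gathered from controls, the arms differ in how often and how closely participants are asked. A difference in recorded events can then arise with no difference in true risk. The trial wants to show a limited side-effect profile against standard care, and section 4 states that no safety board will be set up. This comparison therefore carries much of the trial's safety evidence.

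**Working it through.** The plan states no adverse event rate or capture probability, so there is no figure of its own to reproduce. The check has two parts.

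**1. The sections side by side**

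| Question | Section 3.2.7 | Sections 2.5.2 and 3.1 |
|---|---|---|
| When? | Each counselling session, weekly for 24 weeks: about 24 contacts | Baseline and study end |
| Blinded? | Collector not named; the setting reveals allocation | Yes, by independent or dedicated personnel |
| Which arm? | Natural reading: diet arm (2.4.2, abstract) | Both arms |

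For controls, the only collection times that the article states are baseline and study end.

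**2. Illustration of the size (all rates assumed)**

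Let the true event risk per week be p in both arms and the probability that an event is captured be c. Then over 24 weeks

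P(at least one recorded event) = 1 − (1 − p·c)^24.

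Assume c = 0.9 with weekly contact and c = 0.4 with a single enquiry at study end.

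- p = 0.02, diet: 1 − (1 − 0.018)^24 = 0.353. Control: 1 − (1 − 0.008)^24 = 0.175. With 35 per arm this is about 12/35 v 6/35, Fisher p = 0.17.
- p = 0.05, diet: 1 − (1 − 0.045)^24 = 0.669. Control: 1 − (1 − 0.020)^24 = 0.384. With 35 per arm this is about 23/35 v 13/35, Fisher p = 0.031.
- With 30 per arm, which is 35 less the 14% loss in section 2.6.1, the second case becomes about 20/30 v 12/30, Fisher p = 0.07.

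So the spurious ratio of proportions is 0.353/0.175 = 2.0 or 0.669/0.384 = 1.7. Whether one trial crosses 0.05 depends on the assumed rate and on the number retained.

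A second calculation gives the exact probability that Fisher's test falsely rejects at two-sided 0.05, with 30 per arm. True risk over the whole study is equal in both arms, and detection is 90% on diet:

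| True risk | Control detection 90% | 70% | 50% | 30% |
|---|---|---|---|---|
| 20% | 2.1% (OR 1.00) | 2.9% (1.35) | 6.3% (1.98) | 14.3% (3.44) |
| 40% | 2.6% (1.00) | 6.0% (1.45) | 19.8% (2.25) | 48.7% (4.13) |
| 60% | 2.7% (1.00) | 10.1% (1.62) | 37.1% (2.74) | 77.5% (5.35) |

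With equal detection the odds ratio is 1 and the test keeps its level. The distortion grows with the gap in detection and with the event rate. With rare events and a small gap it is slight.

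**The case against.** The strongest reply is that section 3.2.7 speaks of additional considerations that are also assessed at the sessions. Session-level capture may simply supplement the baseline and study-end visits that both arms attend, and the article does not say that the two sources will be pooled. This stands in part. It makes the bias conditional on session-collected events entering the comparison. It does not remove the conflict over blinding, and nothing in the article keeps those events out of the test in section 2.6.2.

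Several stronger readings are tempting, and the document does not support them:

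- **Controls have no adverse event data.** Section 3.1 does not restrict collection to baseline and study end, and it covers both arms. Controls can have data from those visits.
- **Controls certainly attend no sessions, and dieticians are the collectors.** Both are inferences. Section 2.4.2 speaks of participants without naming an arm, and section 3.2.7 names no collector. The first inference is strong, because controls taught the diet would no longer be a standard-care group. Blinding is doubtful whoever collects.
- **Tolerability is biased in the same way.** It is measured as drop-out, which can be counted in both arms without any session.
- **Repeated events in one person will be tested as independent.** The wording in section 2.6.2 is loose, but proportions may well mean participants with an event. The counting rule is commonly left to the analysis plan.
- **The diet must look worse.** More contact tends to raise recorded events, but participants may under-report harms to the staff who deliver the diet.

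**Conclusion.** The point holds in a limited form. Section 3.2.7 conflicts with sections 2.5.2 and 3.1 on blinding and does not fit the timing in 3.1. If session-collected events are used in the between-group comparison, ascertainment of adverse events and emerging harms is unequal and unblinded. The probable direction is more recorded events on diet, but this is not certain.

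The size rests wholly on assumed rates. For 2% to 5% true risk per week and 90% v 40% capture, it runs from 35% v 18% to 67% v 38% of participants with a recorded event. Only the higher case is significant at 35 per arm, and not at 30 per arm. The conclusion also rests on the inference that only the diet arm attends the sessions.

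This should be fixed but does not threaten the trial's main result. The sample size is based on the neuropathy questionnaire, and the efficacy end points are unaffected.

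**What to change.** 1. Reconcile sections 2.5.2, 3.1 and 3.2.7: state who collects adverse events, when, in which arm, and whether blinded.
2. Base the formal between-arm comparison on participants with at least one event, elicited with the same structured checklist covering the 24 weeks. The blinded assessor asks it at the study-end visit in both arms. Fisher's test with an odds ratio then fits the data.
3. Report events collected at counselling sessions separately and descriptively for the diet arm, and say that they do not enter the test.

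The cost is a short checklist at a visit already planned, plus wording. It needs no further visits or participants. The downside is that fewer diet-arm events enter the formal comparison and that recall over 24 weeks is less complete. That loss now applies equally to both arms. The change belongs before enrolment, because ascertainment cannot be made equal afterwards.
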